#### Data collection method

The instrument for collecting mental health data is the researcher-made questionnaire about smoker men’s knowledge, attitude and practice regarding to second hand smoke in pregnancy. This questionnaire has subscales including knowledge, attitude and practice. Pregnant women will be asked about exposure to SHS before and after intervention. Saline Cotinine will be measured by pregnant women after the intervention using a saliva kit.

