## Plain English summary

Second-hand smoke exposure is a risk factor for the health of pregnant women, and associated with dangers such as preterm labor, rupture of membranes, cesarean delivery, decreased growth, and intrauterine growth retardation, fetal weight loss, and so on. The exposure to smoke is including breathe of smoke from burning cigarette and smoke from exhaling of smokers. Although the prevalence of female smokers is low in Iran, the high prevalence of smoking among men put women at the risk of SHS. The aim of this study was to design an educational intervention on the smoke of SHS in smoker men on the exposure of pregnant wives. This research-based program is designed in three phases, in the first phase of the study; the level of knowledge, attitude, and practice of men regarding SHS will be measured using a questionnaire. The questionnaire will be based on a literature review and experts opinions. In the next phase the educational program will be designed based on the results of the first phase of the study on the level of knowledge, attitude, self-efficacy, and practice of men, as well as a literature review and experts opinions, and the research team will finalize it according to priorities. To follow up the training will be sent reminders messages. Pregnant women will also be trained to protect themselves and support their husbands to quit smoking. The third phase includes the implementation of educational intervention with pretest-posttest with two intervention and control groups. In the pretest phase, questionnaires will be completed by men and the exposure of women to SHS will be achieved as self-reported. Two months after the training in the post-test phase, the questionnaire will be completed again by men. The exposure of pregnant women to SHS and the amount of salivary cotinine will be measured.

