#### Exclusion criteria

The exclusion criterion is not completing the intervention for any reason, the smoker men who are not with their pregnant wives for more than one week, the pregnant termination, and the death of the spouse or immigration and active smoker women and presence of other sources of exposure such as other smokers at home, smoke exposure at work, women’s active smoking, etc.

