## Discussion

Various studies have shown, creating messages that raise awareness and acceptance about the dangers of the second hand smoke in pregnancy and childhood can increase men’s incentive to quit smoking, and that encouraging men to participate and support their wives in prenatal care will push them to quit smoking [17–20]. Another study showed that it could not be expected that with brief intervention alone, exposure to SHS was reduced, rather, to reduce exposure, strategies should be employed to involve parents and other family members in order to have more impact [9]. Evaluation of the exposure to cigarette smoke and its avoidance strategies is a crucial part of the pregnancy care programs [12]. The content of educational interventions should be for both pregnant women and their husbands, and the use of community-based and theory-based interventions creates a framework for programs and attempts to change the smoking culture around pregnant women [6].

The present study provides strong information and data regarding the needs and strategies for reducing the exposure to second hand smoke in pregnant women. Therefore, designing a program, and a review article and updated evidences can lead to avoid pregnant women the exposure to second hand smoke and reducing smoking in smoker men. It can also reduce their medical and treatment costs.

We suppose this program has capacity to integrate into the professionally health care guidelines, so that it can help medical and health care providers pay attention to the important role of the women health, especially during gestational age. The strategies of this program could be important and cost effective, and therefore we hope that the success of such a program is a step forward in improving their health status and men’s participation in pregnant women’s health care programs In designing the present intervention, in addition to training men, training pregnant women will be used to protect themselves as well as to help train smokers to quit smoking. The strength of this intervention was the use of the cotinine index, along with the self-reporting of exposure to cigarette smoke to measure exposure levels.

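### Salivary cotinine is compared at post-test only by an unadjusted t test, although pre-test exposure is recorded and could sharpen the comparison

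*Protocol article*

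**What the plan says.** The Data collection method section gives two timings side by side. On self-report: "Pregnant women will be asked about exposure to SHS before and after intervention". On the biomarker: "Saline Cotinine will be measured by pregnant women after the intervention using a saliva kit" (the first word is evidently a slip for salivary).

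The Plain English summary agrees. At pre-test, "In the pretest phase, questionnaires will be completed by men and the exposure of women to SHS will be achieved as self-reported". Cotinine appears only in the account of the two-month post-test: "The exposure of pregnant women to SHS and the amount of salivary cotinine will be measured". The outcome section on salivary cotinine describes freezing, cold chain and ELISA but gives no timing, and no section mentions a baseline sample.

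The other outcomes are a researcher-made questionnaire score for the men and the women's own count of cigarettes they were exposed to over one week. The Research hypotheses section compares mean cotinine between groups after the intervention. Data analysis names chi-square and the independent t test, with no adjustment. The Discussion states: "The strength of this intervention was the use of the cotinine index, along with the self-reporting of exposure to cigarette smoke".

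**The concern.** The design is described as pretest-posttest, but its only biomarker has no pre-test value. An independent t test on post-test values carries all the between-woman variation in exposure in its error term, including the part that a baseline measure would explain.

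This matters most for cotinine because the other outcomes are self-reported and the groups are treated visibly differently: the control group gets nothing until the end of the study, while women in the intervention group are trained to support their husbands in quitting. Cotinine is the outcome least open to reporting that differs by arm, so precision on it is worth having. The protocol already collects a baseline exposure measure that could supply some, and the named test does not use it.

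**Working it through.** **No figure to reproduce.** The document states no sample size, power, significance level, effect size, standard deviation or correlation. What follows illustrates scale and does not estimate this trial's power.

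**Inputs from the document.** Two randomised groups; cotinine at post-test only; self-reported exposure at pre-test and post-test; an unadjusted independent t test.

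**Assumed inputs.** Two-sided significance level 0.05; 80% power for the unadjusted test; 1:1 allocation; standardised difference d = 0.5 for the sample-size column; correlation rho between the baseline covariate and post-test log-cotinine of 0.3 to 0.7. I take 0.3 for the pre-test self-report and 0.5 to 0.7 for a baseline log-cotinine. Neither comes from the document.

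**Formulas (normal approximation).**
- Residual variance with ANCOVA, relative to the unadjusted test: 1 − rho².
- Power with adjustment, at the sample size that gives 80% without it: Φ[(1.960 + 0.842)/√(1 − rho²) − 1.960].
- Number per arm: 2(1 − rho²)(1.960 + 0.842)²/d². Unadjusted at d = 0.5: 2 × 2.802²/0.25 = 62.8, so 63.

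| rho | 1 − rho² | Variance removed | Power (from 0.80) | Per arm (from 63) |
|---|---|---|---|---|
| 0.3 | 0.91 | 9% | 0.836 | 58 |
| 0.5 | 0.75 | 25% | 0.899 | 48 |
| 0.7 | 0.51 | 49% | 0.975 | 33 |

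For rho = 0.3, for example: 2.802/√0.91 − 1.960 = 0.977 and Φ(0.977) = 0.836; 0.91 × 62.8 = 57.1, so 58 per arm.

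**Chance imbalance.** In standard-deviation units, the difference between arms in a baseline covariate has standard deviation √(2/n). With an assumed 50 per arm this is √(2/50) = 0.20, a 95% range of ±1.96 × 0.20 = ±0.39. An imbalance at that limit shifts the unadjusted post-test difference by rho × 0.39: 0.12, 0.20 and 0.27 SD for rho of 0.3, 0.5 and 0.7. The t test's standard error already allows for such shifts across repeated trials. ANCOVA corrects the one that actually occurs.

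**If a baseline cotinine were added.** The gain depends on the analysis. A change score has relative variance 2(1 − rho), which is 1.4, 1.0 and 0.6 for the same correlations: worse than post-only at 0.3 and no better at 0.5. ANCOVA's 1 − rho² never exceeds 1.

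**The case against.** The strongest reply is that nothing here is invalid. Allocation is random, so the post-only difference in means is unbiased on average, the t test's error rate already covers chance imbalance, and the comparison matches the stated hypothesis, which is about levels after the intervention and not change within a woman. All of this stands. A reader might infer that a chance baseline difference could not be told from an effect; the documents do not support that. Baseline exposure is recorded by self-report, so imbalance can be inspected and adjusted for, though on a weaker measure.

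A reader might also infer that the missing baseline sample lets undisclosed smokers into the trial. The Exclusion criteria section does rule out "active smoker women and presence of other sources of exposure", but it does not say how this is verified, and a condensed article may leave that out. A baseline sample frozen and assayed with the post-test sample would give its result only after the two-month follow-up, so it could not screen anyone before randomisation. The Background also reports that smoking among women in Iran is uncommon. This is not an argument for the change.

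Thirdly, covariates are commonly left to an analysis plan, which is not shown. That would answer a complaint about silence, but this article names the test. If an analysis plan already adjusts for pre-test exposure, the analysis part of this point is met and the article's wording needs aligning.

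Finally, a second saliva sample is not free. It doubles collection and assays, needs frozen storage if batched, and assumes the women attend in person at pre-test, when the document says only that they are asked.

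**Conclusion.** The point holds as one of efficiency. The only objective outcome is measured once, after the intervention, and is to be compared without adjustment although a baseline exposure measure is collected. The comparison is valid; it gives up precision and leaves any realised imbalance in exposure uncorrected.

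The loss cannot be estimated from the document. Under assumed correlations of 0.3 to 0.7, adjustment would remove 9% to 49% of the variance. With the self-report already collected, the low end is the cautious expectation: power of 0.80 would become about 0.84. The higher figures, 0.90 to 0.975, need a correlation of 0.5 to 0.7, assumed here only for a baseline cotinine, and also rest on the assumed 80% start. A reader might take them as this trial's gain, but the document does not support that.

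This is an improvement available at no cost in data collection, not a flaw that undermines the trial.

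**What to change.** 1. In Data analysis, replace the independent t test for cotinine with ANCOVA: post-test cotinine as outcome, group as factor, and pre-test self-reported weekly cigarette exposure as covariate. Use log-cotinine if the values are skewed, as is likely, and say that the effect is then a ratio of geometric means and not the difference in means in the hypotheses. Fix the covariate and the scale before outcome data are seen.
2. State that the pre-test question to the women uses the same one-week cigarette count as the post-test, so that the covariate is defined.
3. In the outcome section and the Discussion, describe the cotinine result as a post-only comparison.

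These three changes cost only wording and one model in the software already planned.

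Optionally, where kits and storage allow, also take a saliva sample at pre-test, handle it like the post-test sample, and use baseline log-cotinine as the ANCOVA covariate, not in a change score. The cost is one more sample and assay per woman, with about two months of frozen storage if both samples are assayed together. It should be justified by precision and not presented as a way to screen active smokers before randomisation.

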##### Data analysis

We will apply X2 and independent T test to analysis our data by using SPSS version 21.

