## Research hypotheses

According to the main purpose of the study, hypotheses will be considered according to the views of health education and reproductive health professionals. The mean score of knowledge, attitude, and practice of smokers after intervention in the intervention group will be more than the control group. The mean of salivary cotinine and the average number of cigarettes that exposed to them during one week in pregnant women after intervention in the intervention group will be less than the control group.

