### Phase I: Designing a questionnaire on knowledge, attitude and practice of smoker men

First, a literature review will be done to select the appropriate model, after interviewing the panel of health education professionals, promotion of health, psychology, epidemiology and reproductive health and reviewing the studies, the questionnaires will be designed based on some of the constructs of the health belief model. The questionnaire consists of the following structures: knowledge, perceived sensitivity, perceived severity, self-efficacy, and behavior. To assess the validity of the questionnaire, a fifteen-person panel of health education professionals, health promotion, psychology, epidemiology and reproductive health will be used and CVR and CVI will be obtained to verify structures. To verify the reliability of the questionnaire, internal consistency with alpha Cronbach will be measured. The questionnaire will be used in the pre-test and post-test of the intervention phase.

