### Phase III: Implementation of educational intervention

In this step a randomized controlled clinical trial will design to assess the efficacy of prepared protocol. Participants randomly will allocate into two groups. In experimental group we will implement our designed protocol, and control group will not receive any intervention, but they follow as same as experimental group. For ethical issues all educational material will offer them at the end of study.

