#### Outcome measures

##### Knowledge, attitude and practice of smoker men

The mean score of knowledge, attitude and practice of smoker men will be measured using a researcher-made questionnaire in the pre-test and post test phase.

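### Pre-test scores and exposure are collected in both arms, but the stated t-test makes no use of them and so gives up precision

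*Protocol article*

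**What the plan says.** The Data analysis section is one sentence: "We will apply X2 and independent T test to analysis our data by using SPSS version 21".

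The Research hypotheses section sets the contrast as a difference between arms after the intervention: "The mean score of knowledge, attitude, and practice of smokers after intervention in the intervention group will be more than the control group". The hypothesis on weekly cigarettes is framed in the same way, with a lower mean expected in the intervention arm.

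Pre-test values of these outcomes are collected:
- Under Outcome measures, the men's scores "will be measured using a researcher-made questionnaire in the pre-test and post test phase".
- Phase I confirms that one instrument serves both occasions: "The questionnaire will be used in the pre-test and post-test of the intervention phase".
- The Data collection method section says: "Pregnant women will be asked about exposure to SHS before and after intervention". The Plain English summary agrees: "In the pretest phase, questionnaires will be completed by men and the exposure of women to SHS will be achieved as self-reported".
- Phase III says the "control group will not receive any intervention, but they follow as same as experimental group", so the control arm has the same measurements.

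Salivary cotinine is the exception. The Data collection method section places it after the intervention only.

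**The concern.** The trial is described as a two-group pretest-posttest design, yet the only test named for means is a two-sample comparison, and the hypotheses are about post-test means. Read together, these sections describe an analysis in which the pre-test plays no part in estimating the effect.

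Two things are at stake. First, part of the post-test spread between men, or between women, is predictable from where they started. A t-test on post-test values leaves that spread in the error term, so confidence intervals are wider and power lower than they need be. Second, if the arms differ by chance at pre-test, part of that difference appears in the post-test comparison and the analysis has no means of removing it. If adjustment is added only after the imbalance has been seen, it becomes a data-driven choice.

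**Working it through.** The article gives no sample size, power, SD or pre-post correlation, so there is no stated figure to reproduce. The inputs below are assumptions: two-sided α = 0.05, 1:1 allocation, equal SD at both times, a standardised difference of 0.5, and ρ of 0.3, 0.5 or 0.7.

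**Variance relative to a post-test-only t-test**
- Adjusted for pre-test (ANCOVA): 1 − ρ²
- Change score: 2(1 − ρ)
- Difference between the two: 2(1 − ρ) − (1 − ρ²) = (1 − ρ)², which is never negative. Apart from the small cost of estimating one slope, a change score cannot be more precise than ANCOVA.

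**Power.** With 80% power by t-test, the effect divided by its standard error is about 1.960 + 0.842 = 2.802. Adjustment divides the standard error's variance down to 1 − ρ² of its value, so the ratio becomes 2.802/√(1 − ρ²):
- ρ = 0.3: 2.802/0.954 = 2.937; 2.937 − 1.960 = 0.977; power about 84%
- ρ = 0.5: 2.802/0.866 = 3.235; 3.235 − 1.960 = 1.275; power about 90%
- ρ = 0.7: 2.802/0.714 = 3.923; 3.923 − 1.960 = 1.963; power about 97.5%

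**Sample size.** At a standardised difference of 0.5, a post-test-only t-test needs 63 per arm for 80% power. The last column is for 63 per arm.

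| ρ | ANCOVA variance ratio | ANCOVA n per arm for 80% | Change-score variance ratio | Change-score power |
|---|---|---|---|---|
| 0.3 | 0.91 | 58 | 1.40 | 66% |
| 0.5 | 0.75 | 48 | 1.00 | 80% |
| 0.7 | 0.51 | 33 | 0.60 | 95% |

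A simulation of 20,000 trials with 63 per arm gave ANCOVA variance ratios of 0.76 (ρ = 0.5) and 0.51 (ρ = 0.7), in line with the formula.

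**Chance imbalance.** With 63 per arm, the SD of the pre-test difference is √(2/63) = 0.178 SD. A difference beyond 0.2 SD in either direction therefore occurs in about 26% of randomisations. In the same simulation, with no true effect, the trials whose pre-test difference exceeded +0.2 SD showed:
- a mean unadjusted post-test difference of 0.14 SD (ρ = 0.5) or 0.20 SD (ρ = 0.7)
- a false-positive rate for the t-test of about 10% or 14%
- an adjusted difference of about 0

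Over all simulated trials, the t-test's false-positive rate was 5.0%.

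**The case against.** The strongest reply is that the analysis sentence names a test but not the variable it is applied to. An independent t-test could be run on change from pre-test, which would use the baseline, and a hypothesis about post-intervention means is compatible with an adjusted estimate. This is also a condensed article, and a fuller plan may specify covariates. That stands to this extent: a reader might infer that the article rules out baseline adjustment, and it does not. What it does is name a method and a contrast, neither of which uses the pre-test. The change-score reading does not rescue the choice, since it is never more precise than ANCOVA and is worse than ignoring the baseline when ρ is below 0.5.

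A second reply is that nothing stated is invalid. That is correct. A reader might infer that the t-test is biased or has an inflated error rate. Over all randomisations it is unbiased and holds 5%. The harm is lost precision, and bias only conditional on an imbalance that has occurred.

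Third, the size depends on an unknown correlation, and at the low end the gain is only from 80% to 84%. This stands. For weekly cigarettes, the inclusion criteria admit only men who smoke daily beside their wives. That restricts the range at pre-test and may lower ρ, so the upper end of the range deserves less weight there.

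**Conclusion.** The point holds as one of efficiency for the knowledge, attitude and practice scores and for self-reported weekly exposure. The stated analysis is valid but leaves collected information unused. Under assumed correlations of 0.3 to 0.7, the variance of the effect estimate could fall by 9% to 49%, which is worth about 4 to 17.5 percentage points of power from a starting point of 80%. These figures rest on ρ, on equal SDs at the two times and on a hypothetical 80%. None of these comes from the article.

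Two stronger readings are not supported. One is that a pre-test imbalance passes in full into the estimated effect. In a post-test comparison only a fraction ρ does on average: a 0.2 SD imbalance contributes 0.06, 0.10 or 0.14 SD at ρ = 0.3, 0.5 or 0.7. The other is that the computed gain extends to cotinine. It has no pre-test value, and its correlation with pre-test self-reported exposure is not given.

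**What to change.** In the Data analysis section, replace the independent t-test for these outcomes as follows.

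- **Knowledge, attitude and practice scores:** linear regression of the post-test score on arm and the same score at pre-test, reported as an adjusted difference with 95% CI.
- **Weekly cigarettes:** the same structure with the pre-test count as covariate, using a count model, a transformation or robust standard errors, because the count may be skewed and may reach zero. The choice should be named in advance, along with the effect measure it yields: a difference, or a ratio for a log-link count model.
- **Cotinine:** a comparison between arms, to which the woman's pre-test self-reported exposure may be added as a covariate. No particular gain should be claimed.

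If a fuller plan already specifies baseline adjustment, the article's sentence should be brought into line with it.

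The cost is two or three sentences. No new data are needed, and the stated software fits a baseline-adjusted comparison. The change should be made before post-test data are seen.

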### Phase II: Designing an educational intervention

The design of the intervention and the target audience’s recognition, at this stage, will be based on a review of the literature, studying the similar studies, as well as information from the questionnaire designed in the previous phase. In this study, the educational package with regard to time limitation of contacts includes lecture sessions (30–60 min), educational pamphlets, animations about second-hand smoke harms, fetus photos, reminiscent text messages and the training of pregnant women to support their husband for reducing smoking. Types of educational messages are listed in Table 1.

**Table 1 Tab1:** Types of educational package messages

*• Educational messages*: Content about cigarette smoke, SHS and its complications presented at a lecture and pamphlet (e.g. SHS causes preterm labor).	
**•** *Functional messages*: Describe the simple steps to quit smoking and protect your wife from smoke presented at a lecture and pamphlet (e.g. put lighter and ashtray away from your reach).	
**•** *Motivational messages*: Includes images and animations (examples: images included in the pamphlets and animations related to cigarettes and its effects).	
**•** *Self-efficacy promotion messages*: Breaking complex behaviors into simple steps, presented in Pamphlet and use the role model at a lecture session (e.g. Simple steps to quit smoking and protective strategies, key sentences about the ability to quit smoking, expressing the experiences of a smoker from the history of smoking cessation and having the ability to quit smoking).	
**•** *Alert or reminder messages*: Message or content to remind you of second-hand smoke complications for pregnancy and embryos (including a picture will be given to the participants to sit at their home in front of their eyes; this photo is “a fetus who asks the father not to smoke” and sending reminders).	
**•** *Supportive messages*: Getting help from pregnant women as “educational co-sponsors” to support their husbands to quit smoking.	

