#### Follow up and maintaining education (fetus photo, SMS reminder, receiving support from pregnant women)

At the end of the lecture, a picture will be given to the participants to sit at their home in front of their eyes; this photo is “a fetus who asks the father not to smoke”. After training, for two months at the end of each week, an alert SMS will be sent to the participants. Pregnant women will be trained to protect against second smoke and support their husbands to quit smoking. Pregnant women will be as “educational co-sponsors”.

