#### Study environment and population

This interventional randomized study will be conducted at health centers of Isfahan, Iran.

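### If the lectures are given to groups of men, the planned independent t-test ignores session clustering in the intervention arm and its standard error is too small

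*Protocol article*

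**What the plan says.** The Data analysis section of the protocol article is one sentence: "We will apply X2 and independent T test to analysis our data by using SPSS version 21". It has no term for session or centre.

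Phase III sets the unit of allocation as the individual, "Participants randomly will allocate into two groups", and the comparison as no treatment: "control group will not receive any intervention, but they follow as same as experimental group".

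Phase II says the package "includes lecture sessions (30–60 min), educational pamphlets, animations about second-hand smoke harms". The training-session section and Table 1 add a former smoker who recounts how he quit, as a role model. The follow-up section then says "At the end of the lecture, a picture will be given to the participants" and that "for two months at the end of each week, an alert SMS will be sent to the participants".

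The setting is given as "This interventional randomized study will be conducted at health centers of Isfahan, Iran". The article does not give the number of men per lecture, of lectures or of centres, or say whether allocation is stratified by centre.

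The Research hypotheses section states every efficacy comparison as a difference in means: the men's knowledge, attitude and practice scores, and the women's salivary cotinine and weekly cigarette exposure. The t-test is therefore the test that carries the conclusions.

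**The concern.** Men who attend the same lecture share that occasion and may share the same role model. If this moves their outcomes together, the observations in the intervention arm are not independent. Controls attend no session, so the correlation sits in one arm only. This is a partially nested design: individuals are randomised, but one arm is then grouped by delivery.

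An independent t-test counts every man as a separate piece of information. With positive within-session correlation it underestimates the variance of the intervention-arm mean, so p-values are too small and confidence intervals too narrow. The error favours declaring the programme effective, and the Discussion hopes to see the programme taken into health care guidelines.

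**Working it through.** The article gives no sample size, significance level, standard deviation, session size or ICC, so there is no figure of its own to reproduce. The check asks how far the stated test could be off under plausible values.

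**Inputs from the article.** Individual randomisation and an untreated control arm (Phase III); lecture-based delivery (Phase II and the follow-up section); independent t-test (Data analysis).

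**Assumed inputs.** Equal arms, equal total variance in both arms, a two-sided 5% level, m = 10 or 20 men per session, ICC = 0.02 to 0.10.

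**Formulas.**
- Design effect in the intervention arm: DE = 1 + (m − 1) × ICC. In the control arm it is 1.
- True over assumed variance of the difference: V = (DE + 1)/2.
- True over assumed standard error: √V.
- True type I error of a nominal 5% test: 2Φ(−1.96/√V).

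**Example, m = 10 and ICC = 0.05.** DE = 1 + 9 × 0.05 = 1.45. V = 2.45/2 = 1.225. √V = 1.107. Type I error = 2Φ(−1.96/1.107) = 7.7%.

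| m | ICC | DE | V | √V | True type I error |
|---|---|---|---|---|---|
| 10 | 0.02 | 1.18 | 1.090 | 1.044 | 6.0% |
| 10 | 0.05 | 1.45 | 1.225 | 1.107 | 7.7% |
| 10 | 0.10 | 1.90 | 1.450 | 1.204 | 10.4% |
| 20 | 0.02 | 1.38 | 1.190 | 1.091 | 7.2% |
| 20 | 0.05 | 1.95 | 1.475 | 1.214 | 10.7% |
| 20 | 0.10 | 2.90 | 1.950 | 1.396 | 16.0% |

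With m = 1 (one-to-one teaching) or ICC = 0, DE = 1 and the error stays at 5%. Over a wider grid, m = 5 to 30 and ICC = 0.01 to 0.10, √V runs from 1.01 to 1.57 and the type I error from 5.2% to 21%.

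**Simulation of the t-test under no effect.** Assumed 60 per arm, sessions of 10, six centres, 6,000 runs per cell (Monte Carlo standard error about √(0.05 × 0.95/6000) = 0.3 percentage points at 5%).

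| Source of correlation | ICC 0.02 | ICC 0.05 | ICC 0.10 |
|---|---|---|---|
| Session, intervention arm only | 6.5% | 7.1% | 9.7% |
| Centre, individuals randomised without balancing | 5.0% | 4.6% | 4.7% |
| Centre, individuals balanced within centre | 4.7% | 4.1% | 3.8% |
| Centre, whole centres allocated | 8.9% | 16.9% | 25.8% |

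The first row agrees closely with the formula. The second and third rows show that leaving out centre does not inflate the error when individuals are randomised. The last row needs allocation of whole centres, which the article does not describe.

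**The case against.** **Group delivery is inferred.** No section says how many men attend a lecture. The plural in "At the end of the lecture, a picture will be given to the participants" is weak evidence, because the same section uses the same plural for a text message sent to each man. This stands, and it makes the point conditional. But a lecture session with a role model, chosen under limited contact time, is most naturally read as group teaching, and nothing describes one-to-one lectures.

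**The ICC may be near zero.** Pamphlets, the photograph kept at home, the text messages and the wife's support work outside the session. Outcomes come two months after training, and cotinine and cigarette exposure are measured in the wife. If one speaker gives every lecture, the speaker adds no variation between sessions. All of this stands as a reason for caution about size, particularly for the women's outcomes. It does not make independence a safe assumption for the men's knowledge and attitude scores, which the lecture targets directly.

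**This is a condensed article.** Session size may be in the full protocol, and its absence here is not the fault. What remains is that the article fixes a particular test, and that test does not fit the delivery it appears to describe.

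**Centre.** A reader might infer from the mention of several health centres that ignoring centre also shrinks the standard errors. The article does not support this. Individuals are allocated, so centre effects fall on both arms, and the unadjusted test is valid or, if allocation is balanced by centre, conservative.

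**Conclusion.** The point holds in conditional form. If the lectures are given to groups and the session ICC is above zero, the independent t-test is anti-conservative. With 10 to 20 men per session and an ICC of 0.02 to 0.10, a nominal 5% test rejects a true null about 6% to 16% of the time, and the true standard error is about 1.04 to 1.40 times the one the test uses. The session sizes, ICCs, equal arms and 5% level are all assumptions.

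A reader might go further and conclude that the trial's standard errors are too small as a matter of fact. The article does not support that: it states neither group teaching nor a session size, and one-to-one teaching or a zero ICC removes the problem. Centre is no part of the error. It is an optional covariate for precision, or a required one if allocation is stratified by centre.

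**What to change.** 1. State whether the lectures are given to groups, and of what size.
2. Record a session identifier for each couple during delivery. Attendance may not be recoverable afterwards.
3. In the Data analysis section, replace the independent t-test with a linear mixed model containing arm, the pre-test value where one is collected, and a random session effect in the intervention arm only. Treat each control as a singleton and use small-sample degrees of freedom.
4. Apply the pre-test adjustment to the knowledge, attitude and practice scores and to self-reported exposure. It cannot apply to cotinine, which the Data collection method section measures only after the intervention.
5. Include centre if allocation is stratified by it; otherwise it is optional.
6. Drop the session term if the lectures are one-to-one.

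The cost is one recorded variable, a change of wording, and wider confidence intervals: about 4% wider at the bottom of the assumed range (√1.09 = 1.044) and about 40% at the top (√1.95 = 1.396), before any gain from the pre-test adjustment. If there are few sessions, the session variance will be poorly estimated. The small-sample degrees of freedom are meant to allow for that, and will widen the intervals somewhat further.
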